### Analysis by subgroups

The intervention effect could be affected by age, sex, educational level and adherence to the application during the study, as well as motivation and lifestyles at the baseline assessment. The same analyses described above will be performed for each of the aforementioned subgroups.

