#### Other variables

Motivation for change, as described by Prochaska and Diclemente, will be assessed at baseline, classified into the different stages of pre-contemplation, contemplation, determination, action, maintenance and relapse. With intervention group participants, app adherence will be measured by the number of logs and days on the device.

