### Blinding

Given the nature of the intervention itself, participants cannot be blinded. However, strategies will be in place to attain the highest level of blinding possible. The researcher making the visit to the intervention group to explain the app will be different from the nurse responsible for taking the measurements and the person in charge of carrying out brief counseling after the baseline evaluation visit. In addition, the researcher responsible for the statistical analysis will not know the group to which the participants belong. To prevent contamination between groups, no additional counseling or reinforcement will be made during the 3-month evaluation visit. In addition, the app will not be available for download until the study is completed.

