### Analysis plan

#### General analysis

Results will be expressed by means and standard deviations for quantitative variables, or by frequency distributions and percentages in the case of qualitative ones. The normality of variables will be tested by means of the Kolmogorov-Smirnov test. When a normal distribution cannot be assumed, we will use the corresponding nonparametric tests. The chi-square test or Fisher’s exact test will be applied to analyze the association between independent qualitative variables. Using the Student’s t-test or the Mann-Whitney U test, the means between the two groups will be compared. The relationship between quantitative variables will be analyzed with the Pearson or Spearman correlation coefficients.

Analysis of the results for the main variable and the secondary variables will be carried out by intention-to-treat. In addition, app adherence will be the subject of a secondary analysis, as described in the results of the EVIDENT II study [66] (< 60 days and > 60 days), and other relevant subgroups will also be analyzed in terms of their physical activity or previous adherence to the Mediterranean diet.

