### Analysis of the effect of the intervention on primary (steps/day) and secondary outcomes

To analyze the changes at 3 and 6 months’ post-baseline in the primary (physical activity - steps/day) and the secondary outcome within the same group, the Student’s t-test or the Wilcoxon test will be used for paired data. The McNemar test will be used for dichotomous variables.

The intervention effect will be analyzed by comparing the changes between IG and CG in blood pressure and secondary variables by using ANCOVA and adjusting for possible confounders. The intervention effect over the period studied will be measured by a repeated measures analysis.

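### App adherence is listed as a subgroup for the between-arm effect, but only the intervention arm has an adherence value, so that analysis has no controls and cannot be run as written

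*Protocol article*

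**What the plan says.** The section Analysis by subgroups says that "The intervention effect could be affected by age, sex, educational level and adherence to the application during the study", and adds baseline motivation and lifestyle to the list. It then prescribes the analysis: "The same analyses described above will be performed for each of the aforementioned subgroups".

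The analyses described above are in the preceding section on the effect of the intervention. There are two main kinds:

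- a between-arm comparison: "The intervention effect will be analyzed by comparing the changes between IG and CG in blood pressure and secondary variables by using ANCOVA", with adjustment for confounders (the sentence names blood pressure, which the article does not list among its outcomes; that is a separate matter);
- changes from baseline "within the same group, the Student’s t-test or the Wilcoxon test will be used for paired data", with McNemar's test for dichotomous variables.

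On who has an adherence value, the section Other variables says: "With intervention group participants, app adherence will be measured by the number of logs and days on the device". The Intervention section issues the smartphone and smartband to the intervention group only. The Blinding section adds that "the app will not be available for download until the study is completed".

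General analysis keeps the main and secondary outcomes on an intention-to-treat basis. Separately, it makes app adherence a secondary analysis split at "< 60 days and > 60 days", with reference to an earlier study. It states no comparator for the two adherence categories.

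**The concern.** Age, sex, education, and baseline motivation and lifestyle are fixed before allocation and exist in both arms, so IG can be compared with CG within each level. App adherence differs on both counts: it is determined after randomization, and it is defined in one arm only. Putting it in the same list and prescribing the same analyses commits the plan to a comparison for which half of the data cannot exist.

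The practical risk lies in what an analyst does on discovering this. The easy substitute is adherers against the whole control group. That sets a self-selected part of one arm against all of the other and gives up the protection of randomization. Because the section presents adherence as something that may alter the intervention effect, such a result could be read as the effect of the app in people who use it.

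**Working it through.** **1. Can the prescribed analysis be run?** Setting the sections side by side:

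| Analysis prescribed for each subgroup | Needs | Available within an adherence stratum? |
|---|---|---|
| ANCOVA of change, IG versus CG | participants from both arms | No: CG has no adherence value |
| Paired t, Wilcoxon or McNemar within a group | one arm, two time points | Yes, in IG only |

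The first row is the one that the plan itself treats as measuring the intervention effect. The second row gives change over time in selected IG participants. It mixes any app effect with the counseling that both arms receive, natural change and selection.

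**2. The plan's own figure.** From Sample size calculation: SD 3847, difference 1850, two-sided alpha 0.05, power 0.80, dropout 15%.

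n = 2 × (1.960 + 0.842)² × (3847/1850)² = 67.9, so 68 per arm; 68/0.85 = 80.

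The stated 80 per group reproduces and is not in question. It supplies the 68 completers per arm used below.

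**3. How misleading could adherers versus all controls be?** Inputs from the protocol: SD 3847 and 68 completers per arm. Assumed, because the protocol gives none of them:

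- the SD of 3847 applies to the change in steps/day;
- 50% or 70% of IG are adherent;
- adherence propensity has correlation ρ with a participant's own step change, from 0 to 0.5;
- participants are independent, and the app has no true effect.

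With adherent share s and z the standard normal quantile at 1 − s, the expected differences from CG are:

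- adherers: +ρ × SD × φ(z)/s
- non-adherers: −ρ × SD × φ(z)/(1 − s)

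Example, s = 0.5 and ρ = 0.3: 0.3 × 3847 × 0.399/0.5 ≈ +921 steps/day. With 34 adherers and 68 controls, SE ≈ 3847 × √(1/34 + 1/68) ≈ 808, so the expected z is about 1.14 and the test rejects roughly 20% of the time.

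Simulation, 4000 trials per row:

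| Adherent | ρ | Adherers − CG | Non-adherers − CG | 5% test rejects (adherers vs CG) |
|---|---|---|---|---|
| 50% | 0 | −11 | −17 | 5% |
| 50% | 0.1 | 303 | −291 | 6% |
| 50% | 0.2 | 596 | −607 | 11% |
| 50% | 0.3 | 899 | −908 | 20% |
| 50% | 0.5 | 1509 | −1533 | 48% |
| 70% | 0 | 5 | 4 | 5% |
| 70% | 0.1 | 177 | −441 | 6% |
| 70% | 0.2 | 383 | −853 | 9% |
| 70% | 0.3 | 565 | −1321 | 12% |
| 70% | 0.5 | 927 | −2219 | 26% |

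Against the target of 1850, the spurious gain in adherers runs from 177/1850 ≈ 10% to 1509/1850 ≈ 82%. The step figures scale with the assumed SD of change; the rejection rates do not depend on it.

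**4. The contrast within IG.** At 50% adherent and ρ = 0.3, adherers minus non-adherers is 899 + 908 = 1807 steps/day with an inert app, close to the full design effect. The split within IG is therefore safe only as description.

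**The case against.** The strongest reply is that little depends on this. The main and secondary outcomes are analyzed by intention-to-treat, adherence is labelled a secondary analysis, and nothing says that its result will be presented as the effect of the intervention. Some of the prescribed tests can still be run, and every size in the illustration rests on inputs that the protocol does not give. All of that stands, and it sets the scale of the point. It does not remove the defect: the between-arm analysis is prescribed by name for a factor that controls cannot have.

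A reader might infer more than the documents support:

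- **That the result must be biased toward benefit.** The direction depends on adherence going with better step change. If it does, non-adherers are biased the opposite way; at zero correlation neither stratum is biased.
- **That the blinded analyst will be unmasked.** The Blinding section says that "the researcher responsible for the statistical analysis will not know the group to which the participants belong". A variable filled in for one arm would reveal the arms if it were opened before the main analysis was finished, but the article does not state the order of analyses, and that is commonly left to the analysis plan.
- **That the 60-day cut is a material flaw.** As printed it places exactly 60 days in neither category. This is a matter of notation.
- **That a complier-average effect, with allocation as instrument and 60 days of use as the treatment, is the natural repair.** It requires that allocation does nothing for those below the threshold. Under the Intervention section they too receive the smartphone, the smartband, the training visit and the app's recommendations, so the assumption is doubtful. For illustration, suppose half reach 60 days with benefit d and the rest gain d/2. The intention-to-treat effect is 0.75d, and the estimator returns 0.75d/0.5 = 1.5d, half as much again as the true effect in compliers.

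**Conclusion.** The point holds as a defect in the stated subgroup analysis. The between-arm comparison within adherence strata has no controls and cannot be carried out as written; this follows from the text alone and needs no assumption. Its likely substitute, adherers against all controls, is non-randomized. Under the assumptions listed in the check, it yields a spurious gain of about 180–1510 steps/day and a rejection rate of about 6–48% with no true effect. These figures illustrate a range and do not predict what this trial will find.

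The consequence is confined to a subgroup analysis. It would be wrong to conclude that the intention-to-treat primary result or the sample size is affected.

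**What to change.** - Delete app adherence from the list in Analysis by subgroups. The baseline factors can stay.
- Keep the adherence analysis in General analysis as an exploratory description within IG, in categories <60 and ≥60 days. Label it explicitly as non-randomized and state that it is not reported as an intervention effect.
- A complier-average analysis is optional only. If added, state the assumption that allocation has no effect below the threshold, why that is doubtful here, and that the estimate may therefore be inflated.

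The cost is a change of wording, with no new data. The loss is that the trial will offer no between-arm estimate of effect by adherence.

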### Sample size calculation

The sample size was estimated for the main variable of the study (Physical activity - steps/day). Assuming a standard deviation of 3847 steps/day [49], a power of 0.8 and an alpha risk of 0.05 in a bilateral test, 80 participants are necessary in each group to detect an increase of 1850 steps/day in the experimental group compared to the control group. This calculation was based on the estimate by Alonso-Dominguez et al. [50]. We assumed a dropout rate of 15% throughout the duration of the study (3 months).

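### Within-arm change tests are repeated in subgroups formed on baseline lifestyle; where the subgroup is cut on the tested outcome's own baseline, regression to the mean makes their null hypothesis false

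*Protocol article*

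**What the plan says.** The section on the effect of the intervention describes two kinds of analysis. The first is change within the same group: for quantitative outcomes the "t-test or the Wilcoxon test will be used for paired data", and for binary ones, "The McNemar test will be used for dichotomous variables". The second is the intervention effect, for which changes in the two arms are compared by ANCOVA.

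The section Analysis by subgroups lists age, sex, educational level and app adherence, "as well as motivation and lifestyles at the baseline assessment". It then states: "The same analyses described above will be performed for each of the aforementioned subgroups". Under General analysis the protocol adds that "other relevant subgroups will also be analyzed in terms of their physical activity or previous adherence to the Mediterranean diet". Physical activity is the primary outcome domain, and Mediterranean diet adherence is a secondary outcome.

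No sentence restricts subgroup inference to the comparison between arms. An alpha of 0.05 is the limit of significance for all analyses.

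**The concern.** A paired test takes zero mean change as its null. If nothing changes, that null is true in a whole, unselected arm. It is not true in people selected because their first reading of the same variable was low or high. Part of an extreme first reading is day-to-day or week-to-week variation, and the second reading is expected to lie nearer the mean. The low stratum therefore appears to improve and the high stratum to worsen, in either arm and without any intervention effect.

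What is at stake is how the subgroup results are read. Significant within-arm gains among the least active or the poorest diet adherers could be taken as showing whom the app helps. This differs from multiplicity and from a missing interaction test: correcting either would leave these within-arm p-values in place, still with a false null.

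**Working it through.** **Inputs from the protocol (Sample size calculation).** SD 3847 steps/day, target difference between arms 1850 steps/day, two-sided alpha 0.05, power 0.8, dropout 15%, and a stated size of 80 per arm.

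**The plan's own figure.** n per arm = 2 × (1.960 + 0.842)² × 3847² / 1850² = 67.9, so 68. Allowing for dropout, 68 / 0.85 = 80. The stated 80 is reproduced, and 68 completers per arm is the right number for the check.

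**Assumptions not in the documents.** The baseline-to-3-month correlation r is taken as 0.6 to 0.9. The subgroup is the lower half of one arm at baseline, 34 people. Baseline and follow-up are bivariate normal with equal means and equal SDs, so there is no true change.

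**Expected spurious change.** The mean of the lower half of a normal variable lies 0.798 SD below the overall mean, so

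spurious gain = 0.798 × (1 − r) × SD.

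The SD of change within that half is SD × √[(1 − r²) + (1 − r)² × (1 − 2/π)]. The expected t statistic is approximately the gain divided by (that SD / √34). The two-sided 5% critical value on 33 degrees of freedom is 2.03.

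| r | Spurious gain, steps/day | SD of change in the half | Approximate expected t | False rejection, noncentral t |
|---|---|---|---|---|
| 0.6 | 0.798 × 0.4 × 3847 = 1228 | 3214 | 2.23 | 58% |
| 0.7 | 921 | 2834 | 1.89 | 45% |
| 0.8 | 614 | 2354 | 1.52 | 32% |
| 0.9 | 307 | 1693 | 1.06 | 18% |

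Simulation under the same assumptions agrees to within about two percentage points: roughly 57%, 45%, 32% and 19%. The upper half shows the mirror-image fall, with about the same rejection rates.

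The rejection rate depends on r and the subgroup size, not on the SD. It therefore applies approximately to MEDAS in MEDAS subgroups as well, as far as a bounded integer score behaves like a normal variable.

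**Contrast.** In the whole arm the paired t-test rejects in about 4–5% of simulated trials. Inside the same low half, the between-arm comparison keeps its level: ANCOVA adjusted for baseline 4.5–5.4%, t-test on change 4.5–5.6%. Both arms regress equally, so the artefact cancels.

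**If the subgroup uses a different activity measure.** Suppose the cut is on IPAQ, the outcome is steps, and IPAQ is related to follow-up steps only through baseline steps, with correlation c to them (also an assumption). The gain becomes 0.798 × c × (1 − r) × SD. For c = 0.3 this is about 368 steps/day at r = 0.6 and 92 at r = 0.9, with rejection of about 10% down to 6%. For c = 0.5, rejection is about 18% down to 8%.

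**McNemar, conditional case.** If MEDAS ≥9 were both the subgroup cut and the dichotomous outcome, nobody starting below 9 could cross downward. One discordant cell would be zero by construction. Five upward crossers give exact p = 2 × 0.5⁵ = 0.0625, and six give 2 × 0.5⁶ = 0.031. The test would then ask only whether at least six people crossed.

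**The case against.** The strongest reply concerns the wording. Analysis by subgroups opens by saying what might affect the intervention effect, so the analyses to be repeated could be the between-arm ones alone. That reading is possible, but it is not what the sentence says: it refers without limit to the analyses described above, and the within-arm tests are among them. App adherence is also on the same list and is measured only in the intervention arm, so its strata have no control members of their own. A purely between-arm reading does not sit easily with that.

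Second, the protocol does not fix the cuts. It does not say whether activity subgroups use accelerometer steps or IPAQ. It measures diet change by total score and gives nine points as the level of good adherence, without naming it as a tested binary outcome or as the subgroup cut. This stands. A reader might infer that McNemar is bound to fail in the diet subgroups, or that the full steps artefact is certain; the documents support neither. What remains is that MEDAS is the only diet questionnaire, so a subgroup on previous diet adherence most naturally shares its baseline score with the outcome.

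Third, both arms receive counseling, so change within one arm never isolates the app. This also stands, and it limits the damage to anyone who interprets the within-arm results. It is no reason to keep tests whose null is false.

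Fourth, a statistical analysis plan may settle cut points and interpretation. It may, but the repetition of the tests is stated here and is not merely left open.

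**Conclusion.** The point holds in a limited form and is worth correcting. As written, the plan runs within-arm tests of change in subgroups formed on baseline lifestyle. Where subgroup and outcome share the same baseline measure, the paired test at nominal 5% would falsely reject in about 57% of trials at r = 0.6, falling to 19% at r = 0.9. If the cut is on steps, the apparent gain is about 1,200 falling to 300 steps/day. These figures rest on the assumed correlation, a near-median split, normality and 68 completers per arm. They shrink considerably for steps in IPAQ-based subgroups.

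A reader might infer that the trial's conclusions are biased or that it is bound to report false subgroup improvement. The documents do not support that. The between-arm comparison, the primary result and the sample size of 80 per arm are untouched, subgroups by age, sex and education are not exposed to this mechanism, and the decisive cuts are not specified.

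**What to change.** In Analysis by subgroups, replace the general repetition of analyses, for subgroups defined by baseline physical activity or diet adherence, with a statement on these lines:

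- Inference rests only on intervention versus control, by ANCOVA adjusted for the baseline value of the outcome.
- For dichotomous outcomes, the 3-month proportions are compared between arms.
- Within-arm change is not tested in these subgroups, or is shown descriptively without p-values.
- Where baseline level is studied as a modifier, it stays continuous and an arm-by-baseline interaction is tested. A baseline covariate with an arm term alone gives one common effect and does not test modification.

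It would help to name in the same place the measure that defines each subgroup (steps or IPAQ for activity, MEDAS for diet). The cost is a few lines of analysis wording, with no new data, participants or visits. All that is lost is a set of within-arm subgroup p-values that could not be interpreted.

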### Secondary analyses

Multiple multivariate regression analysis will be performed to identify the variables with the greatest influence on physical activity changes and the secondary variables analyzed.

All analyses will be carried out with SPSS version 23.0 (IBM Corporation, Armonk, NY, USA) and an alpha risk of 0.05 will be assumed as the limit for statistical significance.

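### Effect modification is to be examined by repeating the tests inside each subgroup at alpha 0.05, which does not test whether effects differ and can let chance differences be read as effect modification

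*Protocol article*

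**What the plan says.** The section on analysis by subgroups opens with a question of effect modification: "The intervention effect could be affected by age, sex, educational level and adherence to the application during the study". It adds the participant's motivation and lifestyle at baseline to these factors. It then fixes the method: "The same analyses described above will be performed for each of the aforementioned subgroups".

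The analyses it points back to are in the section on the effect of the intervention. Changes are tested "within the same group, the Student’s t-test or the Wilcoxon test will be used for paired data", with McNemar tests for dichotomous variables. The two groups are compared "by using ANCOVA and adjusting for possible confounders", and a repeated measures analysis is added.

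The general analysis section extends the list: "other relevant subgroups will also be analyzed in terms of their physical activity or previous adherence to the Mediterranean diet". The section on secondary analyses states, for all analyses, that "an alpha risk of 0.05 will be assumed as the limit for statistical significance".

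Nowhere does the article name a treatment-by-subgroup interaction. The regression under secondary analyses looks for variables that influence the changes and mentions no arm-by-factor term. The section on other variables says that app adherence is measured in intervention group participants, by logs and days on the device.

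**The concern.** Whether an effect depends on a characteristic is a question about the difference between two effects. Testing each stratum on its own answers another question: is the effect distinguishable from zero here? A p-value below 0.05 in women and above 0.05 in men is compatible with identical effects in both. Repeating the within-arm paired tests by stratum is weaker still, because these do not compare the arms.

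The trial is sized for one overall comparison, so each stratum has much less information than the whole. Disagreement in significance between strata is then common even when nothing differs. What is at stake is a report that the app helps one kind of older adult and not another when the data show no such thing. A real benefit in a small stratum can equally be dismissed because that stratum alone did not reach significance.

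**Working it through.** **Inputs from the sample size section.** "Assuming a standard deviation of 3847 steps/day", a difference of 1850 steps/day, two-sided alpha 0.05, power 0.80, 80 per group and 15% dropout.

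**The plan's own figure.** n per arm = 2 × [(1.960 + 0.842) × 3847 / 1850]² = 67.9, so 68 evaluable. 68 / 0.85 = 80. The stated 80 per group reproduces, with overall power 0.80 on 68 completers per arm.

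**Assumptions added here, since the article gives no cut points.** Two levels per factor, equal halves (34 completers per arm in each), participants analysed as independent, normal data, an unadjusted two-sample comparison, and the same true effect of 1850 in everyone.

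**Power in one half.** SE = 3847 × √(2/34) = 933. 1850 / 933 = 1.98. Power is 0.498 by the t distribution (0.509 by the normal approximation).

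**Discordance for one factor.** P(exactly one half significant) = 2 × 0.498 × 0.502 = 0.50. An interaction test at 0.05 gives a false positive 5% of the time.

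**Unequal split.** At 30/70, normal-approximation power is 0.336 and 0.650. Discordance = 0.336 × 0.350 + 0.650 × 0.664 = 0.55.

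**Several factors.** The baseline factors number five (age, sex, education, motivation, lifestyle), or six if baseline activity and baseline diet are counted separately. Each factor re-splits the same participants, so the discordance events share one overall estimate and cannot be multiplied as independent. Simulation with 68 per arm and independent 50/50 factors gives:

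| True effect in everyone | At least one discordant pair, 5 / 6 factors | At least one significant interaction, 5 / 6 factors |
|---|---|---|
| 1850 steps/day | about 84% / 86% | about 23% / 26% |
| none | about 29% / 31% | about 22% / 27% |

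The interaction column agrees with 1 − 0.95⁵ = 22.6% and 1 − 0.95⁶ = 26.5%. With no effect at all, discordance for one factor is 2 × 0.05 × 0.95 = 9.5%. All figures are for one outcome; the plan repeats the tests for the secondary outcomes as well.

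**What an interaction test could detect.** SE of the difference between halves = √2 × 933 = 1320. Detectable at 80% power: 2.80 × 1320 ≈ 3700 steps/day, twice the design effect. Power for a true difference of 1850 between halves is about 29%.

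**App adherence.** It has no value in the control group and arises after randomisation. Neither a between-arm comparison within adherence levels nor an arm-by-adherence term can be formed, so the between-arm part of the instruction cannot be carried out for this factor.

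**The case against.** The strongest reply is that this is a short section in a journal article. Cut points, an exploratory label, multiplicity handling and interaction terms commonly sit in a full protocol or SAP, and their absence is no finding. That is right as far as it goes, and the point does not rest on absence. It rests on a sentence that states a method, and that method does not answer the question posed just before it.

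A reader might infer that the investigators will declare effect modification whenever p-values differ between strata, or that interaction tests are ruled out. The article says neither. It says the analyses will be performed and is silent on how strata will be compared. The supportable claim is that chance differences can be read as effect modification.

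A reader might also compute 1 − 0.5⁶ = 98% for at least one discordant factor out of six. That treats the discordance events as independent, which they are not even when the factors are; about 86% is the figure under the stated assumptions.

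The power figures ignore covariate adjustment, while the plan names ANCOVA. If 3847 is the SD of the analysed steps and baseline is a covariate, a baseline to follow-up correlation of 0.5 to 0.7 (assumed) raises half-sample power to 0.62 to 0.78. Discordance then falls to 47% (2 × 0.62 × 0.38) and 34% (2 × 0.78 × 0.22). That stands as a qualification; both remain far above 5%.

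Finally, an interaction test would seldom detect a realistic difference in a trial of this size. That is true. Its gain is mainly fewer false claims, and an interval that shows how little is known.

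**Conclusion.** The point holds in a limited form. The stated subgroup method does not test whether effects differ. With a common effect of 1850 steps/day, it gives conflicting significance between halves about 50% of the time per factor (34% to 47% under the assumed ANCOVA gains, 55% at a 30/70 split), against 5% for an interaction test. Over five to six factors the figures are about 84% to 86%, against about 22% to 27%, without adjustment. These sizes rest on assumed two-level, mutually independent factors and on the 68 completers per arm implied by the sample size section.

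The primary comparison, the sample size and the intention-to-treat analysis are unaffected, and no stated objective depends on a subgroup claim. The plan should be changed, but the main result of the trial is not at risk from this point.

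**What to change.** Replace the closing sentence of the subgroup section with wording such as: *For each baseline factor (age, sex, educational level, motivation stage, baseline physical activity, baseline Mediterranean diet score), the ANCOVA for steps/day will be refitted with an arm-by-factor term. The interaction estimate and the subgroup estimates will be reported, each with a 95% confidence interval. Differences in effect will not be inferred from separate subgroup p-values. These analyses are exploratory; power for realistic interactions is low, and a non-significant interaction will not be taken as evidence of equal effects.*

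Remove app adherence from the list and report it only as a descriptive analysis within the intervention group, including the split at 60 days already named in the general analysis section.

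The cost is plan wording only. No data are added, and fewer tests are run than now planned. Modelling age, steps and diet score as continuous, or showing the subgroup estimates in a forest plot, would be sensible but is a matter of preference.
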